## Abstract

**Background:**

Relatively little is known about protective factors and the emergence and maintenance of positive outcomes in the field of adolescents with chronic conditions. Therefore, the primary aim of the study is to acquire a deeper understanding of the dynamic process of resilience factors, coping strategies and psychosocial adjustment of adolescents living with chronic conditions.

**Methods/design:**

We plan to consecutively recruit *N* = 450 adolescents (12–21 years) from three German patient registries for chronic conditions (type 1 diabetes, cystic fibrosis, or juvenile idiopathic arthritis). Based on screening for anxiety and depression, adolescents are assigned to two parallel groups – “inconspicuous” (PHQ-9 and GAD-7 < 7) vs. “conspicuous” (PHQ-9 or GAD-7 ≥ 7) – participating in a prospective online survey at baseline and 12-month follow-up. At two time points (T1, T2), we assess (1) intra- and interpersonal resiliency factors, (2) coping strategies, and (3) health-related quality of life, well-being, satisfaction with life, anxiety and depression. Using a cross-lagged panel design, we will examine the bidirectional longitudinal relations between resiliency factors and coping strategies, psychological adaptation, and psychosocial adjustment. To monitor Covid-19 pandemic effects, participants are also invited to take part in an intermediate online survey.

**Discussion:**

The study will provide a deeper understanding of adaptive, potentially modifiable processes and will therefore help to develop novel, tailored interventions supporting a positive adaptation in youths with a chronic condition. These strategies should not only support those at risk but also promote the maintenance of a successful adaptation.

**Trial registration:**

German Clinical Trials Register (DRKS), no. DRKS00025125. Registered on May 17, 2021.

**Supplementary Information:**

The online version contains supplementary material available at 10.1186/s12887-021-02869-9.

## Background

Having a chronic condition (CC) means facing an additional stressor in life. Especially during adolescence, youths are confronted with a range of developmental tasks, e.g., finding a partner, preparing for future family and work life, accepting their own body, which can strongly interfere with the demands of a CC [1]. There is consistent evidence that facing a CC, irrespective of the specific diagnosis, increases the risk for mental health problems, such as anxiety and depression [2, 3]. But focusing only on mental disorders does, on the one hand, not cover the entire spectrum of potential functional limitations experienced in daily life. On the other hand, it neglects potential successful psychosocial adjustment. Including health-related quality of life (HRQoL) as a multifaceted, subjective indicator overcomes these shortcomings and allows getting a more concise picture of the psychosocial situation of these youths. Numerous studies have shown that HRQoL in chronically ill children and adolescents is impaired with small to moderate effect sizes compared to healthy youths [4–6]. Yet, CC as a risk factor is not inevitably associated with a poor adjustment. Considerable interindividual differences can be observed and it seems that the predominant response to the CC is a good adjustment [7]. This leads not only to the question of which characteristics and which processes are involved in maladjustment but also to the question of how to explain and attain a good adjustment. Up to now, the majority of research aims to explain the adverse outcomes and little is known about the emergence and maintenance of positive outcomes in the field of CC. There is evidence that higher age, being female, and higher CC severity are significantly associated with worse HRQoL [4–6] and increased mental health problems [8–10]. These factors only explain a small proportion of the variance, whereas psychological factors, e.g., coping or self-esteem, play a more significant role [1, 3, 7, 11–13]. Within the resilience-in-illness and the positive development framework, a number of resiliency factors, primarily addressed in the context of protective factors in CCs, promote positive adjustment via enhancing positive coping strategies and minimizing the influence of risk factors [14, 15]. Hereby, resiliency refers to the “… ability to cope with life circumstances in a positive way, even under conditions overshadowed by risk, and to develop appropriate coping skills despite unfavorable circumstances” ([16], p. 127). In the context of a CC, high levels of self-esteem, optimism, or self-efficacy proved to be relevant resiliency attributes [14, 17–19]. In addition, the so-called “secondary coping strategies” (focusing on efforts to adapt to the CC), e.g., acceptance, cognitive restructuring, or positive thinking, are considered beneficial [11, 20, 21]. It is well-known that resiliency and coping vary with developmental stage [11, 22] and there is first evidence for a dynamic and reciprocal relationship with HRQoL and mental disorders [23]*.* To sum up, prospective cohort designs are needed to understand the dynamic nature of adjustment in youths with a CC since outcomes as well as its protective and risk factors are not stable but fluctuate over time [11]. In addition, it is necessary to include sensitive developmental transition periods (entry into adolescence; emerging adulthood) with their manifold changes [11].

## Objectives

The primary aim of the project is to get a deeper understanding of the dynamic process of psychosocial adaptation, including intra- and interpersonal resiliency and coping strategies, in the face of CCs in a group of adolescents (12–21 years) with type 1 diabetes, cystic fibrosis, and juvenile arthritis. Hereby, psychosocial adaptation refers to the process of adaptation, while psychosocial adjustment refers to the outcome of this adaptation process [13, 24]. The research questions (Q) and hypotheses are as follows:
Q1. How is the causal relationship between a) resiliency and coping strategies; b) psychosocial adaptation and adjustment? It is hypothesized that resiliency and coping strategies show reciprocal influences, and both precede the psychosocial adjustment.Q2. Does psychosocial adaptation (e.g., resilience factors and coping strategies) play a significant role in psychosocial adjustment beyond the influence of general demographic and CC-related factors? It is hypothesized that psychosocial adaptation is more important in explaining adjustment than the above-mentioned general factors (e.g., age, CC severity, gender). It is further assumed that females, as well as those showing conspicuous mental health screening, exhibit lower scores in psychosocial adjustment and therefore represent a high-risk group.Q3. Depending on general, demographic, and CC-related factors, do adolescents differ in psychosocial adaptation and adjustment? It is hypothesized that adolescents with higher age, female gender, more severe mental health problems and higher CC severity exhibit lower scores in psychosocial adaptation and adjustment.Q4. Depending on general, demographic, and CC-related factors, do adolescents differ in their course of psychosocial adaptation and adjustment over the one-year follow-up period? It is hypothesized that adolescents with higher age, female gender, more severe mental health problems and higher CC severity show a less favorable course of adaptation over the 1-year follow-up period compared to those with younger age, male gender, less severe mental health problems and lower CC severity. Figure 1 displays the conceptual model of the study.

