#### Resources in childhood and youth

Seven of the ten subscales of the Questionnaire of Resources in Childhood and Youth (FRKJ 8–16) are used to assess personal (empathy and perspective-taking, self-efficacy, self-esteem, optimism, and sense of coherence) and social resources (parental and social support, peer-group integration) in children and adolescents [42]. Each subscale contains six items. Participants’ responses are measured on a scale ranging from 1 “never true” to 4 “always true”. A sample item is: “When I set my mind to something, I get it done.”. The reliability of the subscales ranges from Cronbach’s α = .69 to Cronbach’s α = .89 [42].

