#### Coping with chronic health conditions

The German version of the 29-item Coping with Chronic Health Conditions Questionnaire (CODI) is used to assess coping strategies of children and adolescents with CCs [49]. The CODI comprises six domains: acceptance, avoidance, cognitive-palliative, distance, emotional reaction, and wishful thinking. Participants indicate their use of the coping strategies on a 5-point Likert scale ranging from 1 “never” to 5 “all the time” (e.g., “I try to ignore my illness.”). Depending on the domain, the internal consistency of the questionnaire ranges from Cronbach’s α = .69 to Cronbach’s α = .83 [49].

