Regression analyses will be applied to analyze the incremental/additional contribution of adaptation in psychosocial adjustment beyond the influence of general demographic and CC-related factors. HRQoL (total score and subscales’ scores) will serve as dependent variable(s), the sociodemographic, CC-specific risk factors and the psychosocial adaptation will form the independent variables. The analysis on differences in a) resiliency and coping strategies and b) the psychosocial adaptation and adjustment depending on demographic and CC-related factors will be addressed by three multifactorial ANOVAs. To examine differences in the course of psychosocial adaptation and psychosocial adjustment, multifactorial repeated measures ANOVAs will be applied. Before these analyses (Hypotheses 2–4), data will be checked on homoscedasticity, normal distribution of errors and multicollinearity. We will control for overall Covid-19 related distress for all analyses, if there is a significant association with psychosocial adjustment at T1 and/or T2. The analyses will be conducted using R [71–74].

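### Q2 hypothesizes that adaptation matters more than general factors, but the planned regression tests only whether adaptation adds anything to them

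*Protocol article*

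**What the plan says.** Under Objectives, Q2 has two parts. The question is incremental: does adaptation "play a significant role in psychosocial adjustment beyond the influence of general demographic and CC-related factors"? The hypothesis that follows is comparative: "It is hypothesized that psychosocial adaptation is more important in explaining adjustment than the above-mentioned general factors". Its general factors are given by example only: "general factors (e.g., age, CC severity, gender".

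Under Statistical analyses, one analysis serves Q2: "Regression analyses will be applied to analyze the incremental/additional contribution of adaptation in psychosocial adjustment", over and above demographic and condition-related factors. The outcome is health-related quality of life, as total and subscale scores. On the predictors the article says that "the sociodemographic, CC-specific risk factors and the psychosocial adaptation will form the independent variables". It names no comparison between the two sets, no measure of importance and no rule for deciding that one set matters more. It does not mention R².

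**The concern.** The comparative hypothesis and the incremental test answer different questions. The null hypothesis of the test is that adaptation explains nothing once general factors are in the model. Rejecting it is compatible with adaptation being the stronger block, an equal one or the weaker one.

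What is at stake is the sentence that will report Q2. If a significant increment is read as confirming the hypothesis, the study will state that resources and coping outweigh age, gender and disease severity without having compared them. The Discussion presents the incremental contribution of protective factors as a starting point for prevention and intervention, so the stronger wording could be carried into practice.

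**Working it through.** **Inputs from the article.** Target n is 450 (Abstract). This agrees with Sample size: 200 conspicuous + 250 inconspicuous = 450. That target rests on a rule of thumb for structural equation models; no effect size is given for Q2.

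Adaptation scores, counted from Study measures:
- Resources: FRKJ 8–16 gives 7 ("Seven of the ten subscales of the Questionnaire of Resources in Childhood and Youth (FRKJ 8–16) are used"), and FSK-KJ, BSSS, SCS-K-D, SCS-D total and FAS give 1 each, so 12.
- Coping: CODI gives 6 ("The CODI comprises six domains"), ERQ 2, and SSKJ 3–8, CERQ and BFSC 1 each, so 11.
- Together 12 + 11 = 23, or 28 if the self-compassion scale enters as six subscales.

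General factors: 3 are named as examples in the hypothesis. The section on sociodemographic and CC-specific information lists about 20, before registry data. The article does not say which enter.

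**Assumptions.** The article gives no R² values. I take population R² of 0.20 for general factors alone and 0.10 for adaptation alone, with between-block correlation ρ of 0 or 0.3. Each block has one informative composite and the remaining predictors are noise.

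**Step 1: does the increment test separate stronger from weaker?** Joint R² = (0.20 + 0.10 − 2ρ√(0.20 × 0.10)) / (1 − ρ²).
- ρ = 0: joint R² = 0.300. The unique share of adaptation is 0.300 − 0.20 = 0.100, and that of general factors 0.300 − 0.10 = 0.200. f² = 0.100/0.700 = 0.143; noncentrality 450 × 0.143 = 64.3.
- ρ = 0.3: joint R² = (0.300 − 0.085)/0.91 = 0.236. Unique shares are 0.036 and 0.136. f² = 0.036/0.764 = 0.048; noncentrality 21.5.

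The noncentral F distribution gives power of 1.00 at ρ = 0. At ρ = 0.3 it is 0.76 for 23 adaptation scores (with 3, 8 or 20 general factors) and 0.99 for 2 composites with 20 general factors. Simulation of the same settings (600 samples each) gave 100% at ρ = 0, and 77%, 75%, 73% and 99% at ρ = 0.3. So the test is significant in about 73 to 100% of samples although adaptation is the weaker block.

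**Step 2: would comparing raw R² help?** With no true association, expected R² for k predictors is k/(n − 1). At n = 450 the denominator is 449.

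| Adaptation vs general predictors | Expected R² | Gap (points) | Adaptation ahead on raw R² when blocks are truly equal |
|---|---|---|---|
| 23 vs 3 | 5.12% vs 0.67% | +4.5 | 82–99.8% |
| 23 vs 8 | 5.12% vs 1.78% | +3.3 | 72–98% |
| 23 vs 20 | 5.12% vs 4.45% | +0.7 | 50–61% |
| 2 vs 20 | 0.45% vs 4.45% | −4.0 | 0–22% |

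The last column is simulated, with equal true R² from 0 to 0.20. On adjusted R² the share is 44 to 53% in every row, close to the 50% it should be.

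**Step 3: order of entry.** Suppose the R² of general factors, entered first, is set against the increment for adaptation. With equal true R² (0.10 or 0.20) and ρ = 0.3, adaptation then comes out ahead in only 10 to 46% of samples (23 vs 3) or 3 to 14% (23 vs 20), because the shared variance is credited to the first block.

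Entering each block last removes the dependence on order: (R²_full − R²_G) − (R²_full − R²_A) = R²_A − R²_G. The right-hand side still carries the block-size gap of Step 2 unless R² is adjusted or cross-validated.

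**The case against.** The strongest reply is that this is loose wording on a question that does not drive the study. The Q2 question is itself incremental and matches the regression, the sample size is set by the structural equation models, and the way importance is quantified is often left to an analysis plan, which is not shown. The first two observations are correct and limit the weight of the point. The third does not dispose of it: the article states both a hypothesis and the analysis meant for it, and the two do not match as stated.

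A reader might also infer that the plan is tilted towards adaptation, because 23 or 28 scores face a handful of general factors and chance alone would give the larger block more R². The article does not support that. It plans no raw R² comparison and does not fix either block. About 20 general variables are collected, and the adaptation constructs could enter as composites, since the cross-lagged models treat them as latent factors. Depending on these choices the chance advantage is clear, negligible or reversed.

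Nor can one say that the regression could never go against adaptation: comparing the first block's R² with the later increment can easily do so, as Step 3 shows.

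Finally, the article does not state at which wave this regression is run. Inflation from same-wave self-report is therefore only a possibility, and several general factors are self-reported too. Overlap between the quality-of-life and coping scales would have to be inferred from scale names alone.

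**Conclusion.** The point holds as a mismatch between hypothesis and test. Following the article as written, no result of the planned regression can support the claim that adaptation is the more important block, because a significant increment is the usual outcome even when it is the weaker one: about 73 to 100% of samples at n = 450.

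That range rests on the assumed R² of 0.10 and 0.20, block correlation of 0 or 0.3, and 2 to 23 adaptation predictors with 3 to 20 general ones. The logical gap does not depend on these figures. The direction and size of any advantage in a raw R² comparison do depend on unstated choices, so no bias in favour of adaptation is established. The point should be settled before analysis; it does not affect Q1, Q3, Q4 or the sample size.

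**What to change.** Choose one of two routes.

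1. Restate the Q2 hypothesis as incremental: adaptation adds to the explanation of adjustment beyond general factors. This matches the Q2 question and the regression already planned, and costs only the stronger claim.
2. Keep the comparative hypothesis and add a comparison. List the variables in each block and the level at which scales enter (subscale, total or composite). For each block report the unique contribution when entered last, as adjusted or cross-validated R². Bootstrap the difference between the two contributions, and claim greater importance only if the confidence interval excludes zero.

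Route 2 needs no new data. It adds a modest amount of programming, including running the bootstrap together with the planned multiple imputation, and leads to a more conservative claim. Neither route requires a change of outcome or adjustment for the baseline score, which would turn the question into one about change.

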**Fig. 1 Fig1:**
[figure not shown]
Conceptual model of the study

## Methods/design

### Study design

This prospective observational study is part of a consortium (Chronic Conditions in Adolescents: Implementation and Evaluation of Patient-centered Collaborative Healthcare (COACH)) funded by the German Federal Ministry of Education and Research (no. 01GL1740C) that examines the mental health status of adolescents with a CC and examines different approaches to understand and overcome mental health issues [25, 26]. The study received approval by the Ethics Committee of the University of Potsdam (date 02/02/2018, no. 52/2017; date 08/31/2018, no. 37/2018; date 10/22/2018, reference no. 37/2018). Assessments take place starting with the mental health screening in clinical units, followed by two assessment time points over 1 year if adolescents agree to participate in the study: baseline (T1) and 12 months follow-up (T2). Based on the mental health screening for anxiety and depression, participants are assigned into the two parallel groups “inconspicuous” with scores below the cut-off (GAD-7 and PHQ-9 < 7) and “conspicuous” with scores above the cut-off (GAD-7 or PHQ-9 ≥ 7) [27–31]. During the recruitment we have been confronted with the Covid-19 pandemic and several regulations to contain the spread of the SARS-CoV-2 coronavirus. Therefore, we included an additional online survey to monitor the Covid-19 pandemic effects. The Covid-19-specific study received approval by the Ethics Committee of the University of Potsdam (date 04/29/2020, no. 27/2020; date 06/26/2020, reference no. 48/2020). The intermediate Covid-19-specific online survey was first implemented in April 2020 and sent out to all participants that had been included into the study up to this point. Since then, the questionnaire has been being sent to participants consecutively 1 week after completing the questionnaire at baseline (T1). The flow chart of the study design is shown in Fig. 2.

**Fig. 2 Fig2:**
[figure not shown]
Study flow chart

### Study participants

Adolescents between 12 and 21 years with type 1 diabetes, cystic fibrosis, or juvenile idiopathic arthritis are eligible for inclusion.

### Recruitment

Consecutive recruitment for this ongoing trial started in June 2019 in clinical centres. Adolescents with type 1 diabetes, cystic fibrosis, or juvenile idiopathic arthritis are recruited during their regular check-up visits in hospitals, clinics, medical practices, and medical centres across Germany. These clinical institutions all take part in one of the following German patient registries, the National Paediatric Rheumatologic Database (NPRD) [32], the National Diabetes Registry (DPV) [33], or the Cystic Fibrosis (CF) Registry [34]. Eligible patients (and their parents) are informed about the research project by the treating physician at the clinical centre and eligible patients are screened for anxiety and depression. All participants and parents of participants under legal age (< 18 years) provide written informed consent prior to inclusion into the study. Informed consent is sent to the University of Potsdam and all further recruitment activities are conducted by researchers there. In the next step, participants are invited to take part in the prospective online survey, which means that they are contacted by phone and receive an invitation email with the link to the survey. If they do not complete the questionnaire, they are contacted by email and phone at set time intervals and reminded to participate. Furthermore, they receive monthly SMS greetings to increase study adherence. To monitor the Covid-19 pandemic effects, participants are invited to take part in an intermediate online survey. Survey data will be connected with the objective medical background data provided by the patient registries: diagnosis, CC severity, CC duration and CC-specific data, e.g., hemoglobin A1c (HbA1c), forced expiratory volume in 1 s (FEV1), and clinical juvenile arthritis disease activity score (cJADAS). Principles of good research practice, data, and participants’ privacy protection are strictly adhered to. For each successfully recruited participant, the respective clinical unit receives a financial compensation of 75€ for its recruitment effort. Participants receive gift coupons as compensation for their time at T1 (20€) and T2 (30€). The online survey started in August 2019 and has been recruiting participants consecutively since. See Table 1 for preliminary descriptive data on the sample.

**Table 1 Tab1:** Demographics of the preliminary sample

Variables	Total (***n*** = 426)	Inconspicuous (***n*** = 297)	Conspicuous (***n*** = 129)
Gender			
Male	185	141	44
Female	240	155	85
Non-binary	1	1	0
Age			
*M* (*SD*)	15.41 (2.05)	15.36 (2.03)	15.53 (2.11)
Range	12–21	12–21	12–21
Subjective socioeconomic status^a^			
*M* (*SD*)	6.73 (1.38)	6.92 (1.39)	6.30 (1.27)
Scale range^b^	Middle range	Middle range	Middle range
Chronic condition			
Type 1 diabetes	316	214	102
Cystic fibrosis	28	21	7
Juvenile idiopathic arthritis	82	62	20

*Note. M* Mean; *n* Number of participants; *SD* Standard deviation; Last day of data inclusion: 01/06/2021

^a^ Missings: *n* = 16

^b^ Scale ranges from 1 to 10

